## Methods

### Study Design

A prospective, population-based, quality improvement study of before and after design, comprising three phases:

Phase 1: assessment of GPs' and physiotherapists' attitudes and behaviours regarding LBP, observation of usual clinical practice and clinical outcomes of patients recruited in a 6 month baseline period;

Phase 2: a multi-component, quality improvement intervention comprising educational courses and outreach visits led by opinion leaders, regular audit/feedback and mentoring support for participating health care practitioners in addition to installation of computerised and paper-based systems to support the subgrouping for targeted treatment care system in practice;

Phase 3: assessment of GPs' and physiotherapists' attitudes and behaviours regarding LBP, observation of clinical practice and clinical outcomes of patients, recruited in a 12 month period following roll-out of the new care system.

The study design is summarised in Figure 1.

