#### b) Patients' clinical outcomes

A consecutive sample of patients consulting with LBP at each participating practice will be recruited in phase 1 for a period of up to 6 months. As each patient consults with LBP at one of the participating GP practices and is assessed, if their GP enters a previously validated back pain Read Code [2] to indicate the reason for consultation as non-specific LBP, a "pop-up" computer prompt will remind them that the patient is eligible to be invited to participate in the IMPaCT Back study. The GP will inform the patient about the study and ask them if they are willing to receive further information by post. On the same computer pop-up screen the GP will record whether the patient is willing to receive further information about the study, in addition to recording their own clinical impression of the patient's risk of poor outcome (low, medium or high risk of poor outcome). The GP will be able to "opt out" of the computer screen pop-up if they consider the patient not eligible for the study. In phase 1, all patients will receive usual primary care, with referral to other services (including physiotherapy) as usual. There will be no subgrouping for targeted treatment in phase 1, or any specific training or additional resources for assessing and managing LBP patients.

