**Figure 2 F2:**
[figure not shown]
Flow chart of IMPaCT Back study patient recruitment and follow-up

**Table 2 T2:** Outcome Measures for Patients

	Domain	Outcome Measures	Time Point (months)
**Primary**	**Back Pain Disability**	Roland and Morris Disability Questionnaire [37]	0, 2, 6
	**Catastrophising**	Catastrophising (from Coping Strategies Questionnaire) [38]	0, 2, 6
**Secondary**	**Kinesiophobia**	Tampa Scale Kinesiophobia [53]	0, 6
	**Bothersomeness**	Bothersomeness [2]	0, 2, 6
	**Anxiety/depression**	Hospital Anxiety and Depression Scale [54]	0, 6
	**Self-efficacy**	Pain Self-Efficacy Questionnaire [55]	0, 6
	**Illness perceptions**	Musculoskeletal Illness Perceptions Questionnaire [56]	0, 2, 6
	**Health-related quality of life**	Short Form 12 (version 2) [57]	0, 2, 6
	**Individualised**	Goal Scaling [58]	0, 2, 6
	**Global change**	Compared to symptoms at baseline	2,6
	**Back Pain**	Pain intensity: 0-10 numerical rating scales of least and average pain in last 2 weeks and current pain	0, 2, 6
		Duration [59]	0
	**Pain elsewhere**	Other body region pain(s)	0
	**Preference-based health utility**	EQ-5D [60]	0, 2, 6
	**Employment details**	Current employment status	0,6
		Current/most recent job title	0,6
		Work loss due back problem	0,6
		Work performance	0,6
	**Patient satisfaction**	With information received	2,6
		With care received	2,6
		Rating of overall results of care	2,6
	**Health care resource use**	Primary care consultations	6
		Secondary care attendances (NHS and private)	6
		Additional health care practitioners (NHS and private)	6
		**Prescription and over-the-counter medicines and treatments**	**6**

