#### b) Clinical outcomes for patients

A new cohort comprising a consecutive sample of patients consulting with LBP at each participating practice will be recruited in phase 3 for a period of 12 months. The longer timescale in phase 3 is deliberately chosen so that we can study the pattern of use of the subgrouping for targeted treatment systems over time. As time progresses, the use of the new tools and targeted treatment may reduce, as practitioners may tend to go back to previous patterns of practice, and we aim to monitor this.

When the GP enters a relevant back pain Read Code into their clinical computer, the pop-up screen will include the same items as in phase 1 plus the brief (6 item) subgrouping tool, which, once completed, will yield a targeted treatment recommendation for the GP and patient to use to inform their decision-making. Similarly, if the patient is referred to physiotherapy, their assessment at the first visit with the physiotherapist will include use of the subgrouping tool (9 item version), which will yield a recommendation about targeted treatment.

Patient recruitment in phase 3 will be the same as the procedures described for phase 1. Participants who consent to further contact will receive a follow-up questionnaire at 2 months and 6 months (see figure 2). Those patients who reconsult in phase 3, who have previously been invited to take part in phase 1 will not be re-invited. The same patient outcome measures as phase 1 will be used in phase 3 (see Table 2).

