#### Clinical outcomes for patients

The primary outcome measures of patient benefit will be back pain-related disability (measured on the RMDQ [37] and pain catastrophising (measured on the catastrophising subscale of the Coping Strategies questionnaire [38] at 6 month follow up. Primary analysis of the patient data will follow the principles of "intention to treat", to compare outcomes of patients in phase 1 (pre-intervention) to those of patients in phase 3 (post-intervention). A "per-protocol" analysis, based on the evaluation of phase 3 patients who were treated with strict adherence to the subgrouping tool allocation rule (versus all phase 1 patients) will be carried out as a secondary comparison. Estimates of treatment effects, i.e. comparative outcomes for phase 1 (pre-intervention) versus phase 3 (post-intervention), with 95% confidence intervals will be calculated using linear regression (for numerical outcomes) and logistic regression (for categorical outcomes). Analyses will be carried out both unadjusted and adjusted for baseline imbalances in certain variables i.e. age, gender and baseline values of key outcomes. Statistical adjustment is necessary as this is an observational, before and after study design, and thus open to the possibility of confounding bias; adjustment will ensure parity of key baseline patient characteristics across phases 1 and 3. Analyses will be carried out at each patient follow up time point (2 and 6 months) for primary and secondary outcome measures; the primary endpoint is 6 months. Analyses will be performed on available data, and on imputed datasets based on the method of multiple imputation [47]. We will use STATA and SPSS for the analyses.

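### The adjusted phase comparison omits prognostic variables the study already collects and has no check for the unmatched half of the phase 3 recruitment year

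*Protocol article*

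**What the plan says.** Under Data analysis, Clinical outcomes for patients, the phase 1 and phase 3 cohorts are compared by linear or logistic regression. The models are run unadjusted and "adjusted for baseline imbalances in certain variables i.e. age, gender and baseline values of key outcomes". The section accepts that a before-and-after design is open to confounding, then states that "adjustment will ensure parity of key baseline patient characteristics across phases 1 and 3".

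The recruitment windows differ in length. Study Design gives "clinical outcomes of patients recruited in a 6 month baseline period". The phase 1 patient section says patients "will be recruited in phase 1 for a period of up to 6 months", and the phase 3 section says they "will be recruited in phase 3 for a period of 12 months". The reason given is "The longer timescale in phase 3 is deliberately chosen so that we can study the pattern of use of the subgrouping for targeted treatment systems"; season is not mentioned. The phase 3 section also says that patients already invited in phase 1 are not invited again if they reconsult.

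Table 2 records episode duration and pain in other body regions at month 0. The analysis section for practitioners compares GP risk ratings with the patients' own questionnaire answers to the subgrouping tool, before and after the intervention, so a questionnaire-based risk group should exist in both phases.

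**The concern.** Without a concurrent control, the credibility of the phase contrast rests heavily on the adjusted model. Two sources of difference between the cohorts fall outside it.

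- **Case mix.** The rule against re-invitation removes some persistent or recurrent consulters from phase 3, and phase 1 has no matching exclusion. Duration or prior course could therefore differ by phase, possibly in favour of phase 3. Duration is measured but not adjusted for. Risk group drives the sample-size reasoning, yet it is not a named covariate either.
- **Season.** Phase 3 spans a whole year and phase 1 about half of one. A seasonal difference in 6-month outcome that the baseline values do not explain becomes part of the estimated effect.

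At stake are the size of the estimated effect and the error rate of its test, for an overall effect of about 1 RMDQ point.

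**Working it through.** **Inputs from the article (Sample Size, Patients):** 1000 patients, 20% loss to follow-up, phase ratio 1:2, SD 5, two-sided 5%, and an overall target of about 0.2 SD or about 1 RMDQ point.

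**The plan's own figures.**
- Subgroup: 50 against 100 patients, difference 2.5, SD 5. The normal approximation gives 82% power, consistent with the stated figure of about 80%.
- Overall: 1000 × 0.8 = 800 analysed, or 267 and 533 at 1:2. SE = 5 × √(1/267 + 1/533) = 0.375. Detectable difference at 80% power = (1.96 + 0.84) × 0.375 = 1.05 points (0.21 SD), which matches the stated values. Power for exactly 1 point is Φ(1/0.375 − 1.96) = Φ(0.71) = 76%.

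**Season (assumed range).** Let S be the difference in mean 6-month RMDQ, after the listed adjustment, between calendar months that phase 1 covers and months it does not. With even recruitment, a 6-month phase 1 matches half of phase 3, so bias b = S/2. If phase 1 runs for less than 6 months, the unmatched share is larger. Type I error = P(|Z + b/SE| > 1.96). For S = 1, b/SE = 0.5/0.375 = 1.33, and 1 − Φ(0.63) + Φ(−3.29) = 0.27.

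| S (points) | Bias (points) | Type I error |
|---|---|---|
| 0.5 | 0.25 | about 10% |
| 1 | 0.5 | about 27% |
| 2 | 1.0 | about 76% |

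**Case mix (assumed range).** If an omitted factor differs in prevalence by Δ between phases and shifts 6-month RMDQ by g points after the listed adjustment, bias = Δ × g.
- Δ = 10 percentage points and g = 1, 2 or 3: bias 0.1, 0.2 or 0.3 points; type I error about 6%, 8% or 13%.
- Δ = 15 percentage points and g = 3: bias 0.45 points; type I error about 22%.

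**Cost of matching calendar months.** Restricting phase 3 to the phase 1 months leaves about 267 against 267. SE = 5 × √(2/267) = 0.433. Detectable difference = 2.80 × 0.433 = 1.21 points. Power for 1 point = Φ(1/0.433 − 1.96) = Φ(0.35) = 64%. A season indicator in the full model costs the same: the variance of the phase effect rises by (0.433/0.375)² = 1.33.

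**Linear calendar time.** For assumed gaps of 0 to 12 months between phases, its correlation with phase is 0.82 to 0.96 and the variance inflation about 3 to 12. It cannot usefully be separated from phase.

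All these figures use SD 5 and no precision gain from covariates. The article gives no SD for catastrophising, so no figure is computed for that outcome.

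**The case against.** The strongest reply has five parts.

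- **Adjustment is not the only safeguard.** The same practices, consecutive sampling, recruitment procedure and outcome measures apply in both phases. Referral rates and waiting times are monitored monthly. The Discussion undertakes to track national and local changes and concedes that attribution may not be possible. This stands: a reader might infer that the design has no other protection, and the article does not support that. Monitoring is not linked to any analysis, however.
- **The parity sentence concerns only key characteristics.** It follows the named list and an admission of possible confounding, so it need not claim balance on everything. This stands in part; the verb is still too strong for what regression on a short list can do.
- **The undefined outcomes in the list may cover more.** Table 2 places "Current employment status" among the secondary measures at months 0 and 6, so employment may already be included and is not counted here as an omission. The risk-subgroup comparisons described under Sample Size already condition on risk group; the overall comparison does not.
- **The seasonal effect is hypothetical, and baseline values absorb part of any raw seasonal difference.** Both are correct. Half of the raw difference is the bias of the unadjusted contrast; only the part left after adjustment matters for the adjusted one, and S is defined that way above.
- **Covariates and sensitivity analyses belong in an analysis plan.** For a missing detail, yes. Here the article states the covariate list in closed form and makes a claim about what it achieves.

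**Conclusion.** The point holds as a cheap improvement to the stated analysis. The covariate list leaves out episode duration, pain elsewhere and questionnaire-based risk group, and the re-invitation rule gives a concrete reason why the cohorts could differ. The unequal windows mean that about half of any residual seasonal difference enters the phase contrast. Under the assumed ranges the bias runs from 0.1 point (a modest case-mix shift) to 1.0 point (a 2-point residual seasonal difference), against a design target of about 1 point.

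A reader might infer that both primary outcomes are shown to be biased. They are not: the article gives neither a seasonal nor a case-mix effect, so size and direction are unknown. Nor would a calendar term rescue the design. Month of year can be examined because phase 3 repeats the phase 1 months, but secular trend cannot be separated from phase and remains the limitation that the Discussion concedes.

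**What to change.** 1. Add episode duration, pain elsewhere and questionnaire-based risk group to the prespecified adjusted model for the 6-month comparison. The article indicates that all three are collected, so the cost is wording.
2. Add a sensitivity analysis limited to phase 3 patients recruited in the same calendar months as phase 1. State its cost: detectable difference 1.21 against 1.05 points, and power for 1 point about 64% against 76%.
3. Do not put a season term in the primary model by default, since it carries the same loss of precision against a bias of unknown size. Do not use linear calendar time.
4. Replace the parity claim with wording such as: adjustment *will reduce confounding by the measured variables*. Keep secular trend as a stated design limit.

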#### Determining the cost-effectiveness of subgrouping for targeted treatment

Consideration of cost-effectiveness for any intervention or policy change requires an incremental approach, where the focus of analysis is on the joint estimation of the *differences *in costs and benefits between the new process (in this case, phase 3 following the implementation of subgrouping for targeted treatment systems) and the standard process (phase 1).

The primary health economic analysis will focus on the estimation of incremental cost-utility from an NHS perspective, in line with current national guidelines [39]. Accordingly, the appropriate cost components for the base case analysis will consist of all items of back pain-related resource use within the NHS. Quality-adjusted life years (QALYs) will be calculated by applying area-under-the-curve techniques to EQ-5D scores at baseline, 2 months and 6 months [48], assuming linear interpolation between consecutive data collection points. Differences (phase 3 minus phase 1) in costs and QALYs will be expressed using the incremental cost-per-QALY ratio, which provides an estimate of the additional cost required to gain each additional unit of outcome (1 QALY is interpreted as 1 year spent in full health). The incremental ratio is merely a point estimate and, therefore, it is necessary to address uncertainty. In line with current recommendations, uncertainty will be addressed using bootstrapping techniques, cost-effectiveness planes and acceptability curves [49,50]. As with the clinical outcomes for patients multiple imputation techniques will be used to address the issue of incomplete data [47].

To explore the robustness of our findings, a number of sensitivity analyses will be performed. Data collected as part of this study will enable other perspectives to be considered with regard to the estimation of cost-effectiveness. Moving beyond health care resources attributable to the NHS, a broader 'societal' perspective will incorporate the indirect costs of reduced productivity at work due to low back pain and also costs incurred within the private health care sector. A second sensitivity analysis relating to costs will incorporate generic resource use, rather than just those relating to back pain. With regard to outcome valuation, an alternative UK-derived preference-based measure of health status, the SF-6D, will be considered [51]. Finally, a complete-case analysis will be performed to assess the influence of missing data and the value of adopting multiple imputation methods.

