i) Patient case-based discussion: depending on progress and on availability within the practices, we aim to facilitate further group-based practice meetings to focus on patient care, using a patient as an example to show the potential benefits of the sub-grouping for targeted treatment approach in practice. These will be led by a physiotherapist to whom the GP practice refers patients, in order to facilitate patient-based communication between the practice and the associated physiotherapy services.

j) Funding support: As well as the additional funding to support the GP link for the study in each practice (one clinical session per month), each practice will also be given £10 per patient identified, in acknowledgement of the small increase in time that it takes to determine eligibility of patients, to mention the study to the patient, and to complete the 6-item version of the sub-grouping tool.

k) Offers of additional one-to-one or small group educational meetings: each GP practice and GP will be offered further contact with a GP lead in the study team and the study co-ordinator, at regular intervals throughout phase 2 and 3 to review the use of sub-grouping tool, the aims of the study, the targeted treatments or any other study related issue.

Features of the intervention with physiotherapy services and physiotherapists:

a) Pre-training programme reflective activities/reading.

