b) Stepped education and training programme consisting of a 3 day course for those delivering the targeted treatment for patients classified as at low and medium risk of poor outcome, including use of the 9-item subgrouping tool, identifying and managing patients with physical obstacles to recovery, best practice for LBP and nerve root pain. A further 6 days of training for those physiotherapists treating patients at high risk of poor outcome. These additional 6 days focus on identifying and managing psychological obstacles to recovery and development of skills through role play, case discussion, audio and video training materials and simulated patients. The training programme is supplemented with comprehensive manuals but is designed to be as experiential, skills-based and interactive as possible and includes discussion of operational aspects of the study. Funding support to cover backfill for time taken out from clinical practice for the purposes of training will be provided and training linked into Continuous Professional Development plans for individuals through negotiation with physiotherapy service managers.

c) Individual feedback and review in monthly mentoring sessions over 12 months following the training programme, the first six months led by the training leads and the second six months by senior physiotherapists and IMPaCT Back participants within the PCT. This was included as ongoing mentoring is likely to be the most effective way of consolidating and further developing knowledge, skills and confidence in the new subgrouping for targeted treatment system.

d) The subgrouping tool integrated within the physiotherapy assessment for patients with back pain and the targeted treatment pathways embedded into the ongoing care pathways for patients.

e) Educationally influential practitioners (opinion leaders) leading the training and mentoring programme, including a consultant clinical psychologist, consultant physiotherapist specialising in pain management, an extended scope physiotherapist in a spinal specialist role, a consultant rheumatologist, a GPSI and a disability advisor.

f) Support for the initiative by key leads within the organisation (Primary Care Trust), including the Chair of the PCT and physiotherapy service managers.

g) Study pack of all study information and documentation.

h) Study newsletter to provide feedback to the participating physiotherapists on the progress of the study.

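### The economic section does not carry over the adjustment that the plan calls necessary, and its costing does not capture the new system's set-up and support costs

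*Protocol article*

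**What the plan says.** **Estimation.** Under Determining the cost-effectiveness of subgrouping for targeted treatment, QALYs come from "applying area-under-the-curve techniques to EQ-5D scores at baseline, 2 months and 6 months", with linear interpolation. The result is then defined: "Differences (phase 3 minus phase 1) in costs and QALYs will be expressed using the incremental cost-per-QALY ratio". Uncertainty is handled by bootstrapping, cost-effectiveness planes and acceptability curves. The one method expressly carried over from the clinical analysis is multiple imputation.

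Under Clinical outcomes for patients (Data analysis), the plan states: "Statistical adjustment is necessary as this is an observational, before and after study design, and thus open to the possibility of confounding bias". It adds: "Analyses will be carried out both unadjusted and adjusted for baseline imbalances in certain variables i.e. age, gender and baseline values of key outcomes". On scope it says: "Analyses will be carried out at each patient follow up time point (2 and 6 months) for primary and secondary outcome measures". Table 2 lists EQ-5D and health care resource use among the secondary measures.

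**Costs.** The base-case rule is that "the appropriate cost components for the base case analysis will consist of all items of back pain-related resource use within the NHS". The phase 1 section on outcomes for cost-effectiveness lists attendances, consultations, medicines and over-the-counter treatments, taken from medical records and the 6-month questionnaire and priced at published national average unit costs. The matching phase 3 section says that collection follows the phase 1 approach and covers the 6 months after each participant's first consultation.

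The section on the multi-component quality improvement intervention describes resources of another kind:
- 3 days of physiotherapist training, with 6 more for those treating high-risk patients. "Funding support to cover backfill for time taken out from clinical practice for the purposes of training will be provided".
- Monthly mentoring for 12 months after training.
- A funded link-GP session each month in each practice.
- A payment: "each practice will also be given £10 per patient identified".
- Further funding if demand for physiotherapy rises.

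**The concern.** The cost-per-QALY ratio answers objective (iv) of the study. Two features of its definition put it at risk.

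First, the economic comparison uses the same two cohorts, recruited at different times, for which the clinical section says adjustment is needed. A QALY computed as an area under the curve includes the baseline score. A baseline EQ-5D difference between phases therefore enters the QALY difference directly, and enters again to the extent that it persists at follow-up. Bootstrapping describes sampling error and imputation deals with missing data; neither removes a baseline imbalance.

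Second, the comparison is between a new process and a standard one, but the costs are those of care received by individual patients. Resources spent on practitioners to create and sustain the new process are not recorded that way. Phase 1 by design has no specific training or extra resources, so anything missed falls on phase 3 alone and makes the new system look cheaper than it is.

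**Working it through.** The plan states no economic sample size, cost or QALY value, so there is no figure of its own to reproduce. The check has three parts.

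**1. How far a baseline imbalance moves the QALY difference.** Input: EQ-5D at 0, 2 and 6 months, linear interpolation. Trapezoid weights in years:
- Baseline: (2/12)/2 = 0.083
- 2 months: (2/12)/2 + (4/12)/2 = 0.250
- 6 months: (4/12)/2 = 0.167
- Sum: 0.500

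An imbalance d shifts the unadjusted difference by 0.083d if confined to baseline and by 0.5d if it persists undiminished. The values of d and the £20,000 per QALY are assumptions.

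| d | Baseline only | Fully persistent | Value at £20,000 per QALY |
|---|---|---|---|
| 0.02 | 0.0017 | 0.010 | £33 to £200 |
| 0.05 | 0.0042 | 0.025 | £83 to £500 |

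**2. Whether the clinical adjustment reaches the ratio.** The clinical section covers outcome measures at each follow-up point, 2 and 6 months. That can include EQ-5D scores at those times. The QALY is a different quantity, built across three time points including baseline. Neither it nor the ratio is listed in Table 2, and the economic section, which defines both, names no adjustment.

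**3. Whether set-up and support costs can enter the phase 3 total.** Collection is per patient, begins at consultation, lasts 6 months and mirrors phase 1. Training precedes consultation and belongs to no patient. National average unit costs would not carry this study's own training. The four sensitivity analyses are a societal perspective, generic resource use, SF-6D, and complete cases; none adds these items.

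Counts from the document:
- Training: 20 physiotherapists (planned minimum) × 3 to 9 days = 60 to 180 days. The upper end assumes that all take the extra 6 days.
- Link GP: 7 practices × 12 months of phase 3 = 84 sessions.
- Mentoring: 20 × 12 = 240 physiotherapist attendances; length not stated, so not costed.
- Payment: £10 per patient identified, only part of it for care.

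Denominators: 2,700 consulters a year (the plan's minimum), or 1000 × 2/3 = 667 phase 3 recruits under the 1:2 ratio. Unit costs are assumed: £100 to £300 per training day, £150 to £300 per GP session.

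| Item | Per consulter (2,700) | Per recruit (667) |
|---|---|---|
| Training: 60 × £100 = £6,000 to 180 × £300 = £54,000 | £2 to £20 | £9 to £81 |
| Link GP, counted in full: 84 × £150 = £12,600 to 84 × £300 = £25,200 | £5 to £9 | £19 to £38 |

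The system serves all eligible consulters, so the first column is the fairer one. Spreading training over more than one year would lower its share further; mentoring would add to the total.

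**The case against.** The strongest reply is that both limbs rest on silence in a condensed article. Four parts of it need an answer.

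- **A reader might infer that the plan specifies raw differences.** It does not. The economic section says how differences are expressed and speaks of estimating differences in costs and benefits jointly, which is compatible with regression. The covariates of such a model could stand in an analysis plan that is not shown. Nor does the plan call the design confounded; it says that the design is open to that possibility. What remains is that the article sets out the economic method in some detail and imports imputation by name, yet does not extend to the ratio a step that it calls necessary elsewhere.
- **A reader might infer that the cost rule leaves out everything the new system costs to run.** It does not. Extra physiotherapy contacts, GP consultations and referrals are back pain-related NHS resource use. Table 2 records additional practitioners, and the physiotherapy case report forms record the number and length of sessions. Adding the extra physiotherapy funding on top would count the same contacts twice.
- **Some payments are partly for research.** The £10 also covers determining eligibility and mentioning the study, and the link GP carries communication about the study. Charging these in full to phase 3 would bias the ratio against it. This stands.
- **The rule is inclusive and the list of cost drivers is open-ended.** True, and nothing expressly excludes training. But an inclusive rule does not help when the stated collection is per patient, follows phase 1 and starts at consultation.

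**Conclusion.** The point holds in a limited form. The economic section does not state that cost and QALY differences will be adjusted, although the plan's own reasoning calls for it and the QALY contains a baseline value. Its cost rule and data collection do not capture training, backfill, mentoring, or the care-related part of link-GP time and the per-patient payment, and no sensitivity analysis does so.

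The direction of the first effect is unknown; the second favours phase 3. Sizes are illustrative only: every EQ-5D imbalance, unit cost and value per QALY above is assumed, and the £500 figure needs an imbalance of 0.05 that does not fade over six months. Per eligible consulter the delivery costs are modest, but they fall on one phase only and may matter if the incremental cost is small. This should be put right; it does not invalidate the study.

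**What to change.** - **Adjustment.** State that incremental QALYs and costs will be estimated by regression within each bootstrap and imputed dataset. Adjust QALYs for baseline EQ-5D, and both QALYs and costs for the covariates already named in the clinical section (age, gender, baseline values of key outcomes). Report unadjusted results alongside.
- **Costs.** From study budget records, add to phase 3 the training cost (annuitised and spread over all eligible consulters), backfill, mentoring and the care-related share of link-GP time and the per-patient payment. Report the ratio with and without these items. Leave out research-only payments, and do not add physiotherapy capacity funding to contacts already costed per patient.

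No new patient data are needed: baseline EQ-5D is already collected. The price is some extra costing and analysis, a judgement on how to split mixed payments that should be written down in advance, and a ratio that may look less favourable.
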